# Efficacy of different-frequency TEAS on acute pain after the total knee arthroplasty: a study protocol for a parallel group randomized trial

**DOI:** 10.1186/s13063-019-3379-3

**Published:** 2019-05-29

## Abstract

**Background:**

Total knee arthroplasty (TKA) is an optimal option for patients with middle-to-end-stage knee osteoarthritis. However, the management of postoperative acute pain remains inefficient. Transcutaneous electrical acupoint stimulation (TEAS) is a nonpharmacological method to manage postoperative acute pain. Different frequencies of TEAS have been tested using varying parameters, but the optimal analgesic frequency remains controversial. The aim of this study was to explore the optimal analgesic frequency of TEAS for treating acute pain after the primary unilateral TKA.

**Methods/design:**

This is a double-blind, randomized controlled trial. A total of 156 patients are randomly assigned to: G1, 5 Hz TEAS; G2, 100 Hz TEAS; G3, mixed TEAS (alternative use of daily 5 Hz and 100 Hz TEAS) and G4, placebo TEAS. In the G1, G2 and G3 groups, TEAS is conducted at acupoints SP9 and GB34 of the leg that was operated on (at a wave of continuous, balanced and asymmetrical biphasic square, with a pulse width of 200 μs, and a strong but comfortable current) for 30 min prior to a 30-min rehabilitation session per day for 2 weeks. In G4 group, TEAS is delivered at a strong but comfortable current for 30 s, then the current is gradually decreased to none over the next 15 s. The primary outcomes are measured before surgery, at baseline (POD 3, before TEAS intervention), week 1 and 2 after TEAS intervention with the Numeric Pain Rating Scale and The American Knee Society Score. The secondary outcomes include: (1) Active range of motion of the knee that was operated on; (2) Surface electromyography of both quadriceps; (3) Modified 30-s sit to stand test; (4) Additional usage of analgesia; and (5) SF-36. The additional outcomes include: (1) Patients’ satisfaction rate; (2) Patient’s expectation rate; and (3) Incidence of analgesia-related side effects. To test the blinding of participants and assessors, they are asked to guess whether the subjects received active or placebo TEAS within 5 min after the latest intervention. The safety and financial cost of TEAS are assessed.

**Discussion:**

Mixed TEAS has more favorable effect on acute pain control than the placebo or 5 Hz or 100 Hz TEAS.

**Trial registration:**

ChiCTR1800016347. Date of registration was 26 May 2018. Retrospectively registered.

**Electronic supplementary material:**

The online version of this article (10.1186/s13063-019-3379-3) contains supplementary material, which is available to authorized users.

## Background

### The need for total knee arthroplasty

Osteoarthritis of the hip and knee ranks 11th among the 291 causes of disability, and 38th highest among disability-adjusted life years globally [1]. The age-standardized prevalence of global knee osteoarthritis (KOA) is 3.8%, higher in elderly women [1, 2]. The optimal treatment for middle-to-end-stage KOA is total knee arthroplasty (TKA) [1, 2] which can relieve pain, recover function and improve early stage quality of life (QoL) of KOA patients [2, 3]. The therapeutic methods for middle-to-end-stage KOA have been gradually redefined, TKA of which will remain at hand in the next few decades [4]. In 2012, more than 670,000 cases of TKA were accomplished in the USA alone [5], 94 to 97% of which were operated on for KOA [2].

### Acute pain after the TKA

Surgery is the second most common cause of persistent pain [6]. Though half of all TKA patients report postoperative pain relief [7], 44% of them still suffer continued pain at 3–4 years after the operation [6]. Inadequate post-TKA pain control can lead to adverse events [8], like knee stiffness, infection, deep venous thrombosis [5, 9], and undermine the patients’ ability to perform physical activities, like stair-climbing and heavy manual work [10]. The post-TKA pain also reduces the patients’ satisfaction with this surgery [11] in as many as 18.2% [12]. It can be said that recently developed interventional and preventive strategies have all failed to effectively control the post-TKA pain [13].

### Side effects of analgesic drugs

There are multiple ways to control post-TKA pain [14]. “The panel recommends that clinicians offer multimodal analgesia…combined with nonpharmacological interventions, for the treatment of postoperative pain…(strong recommendation, high-quality evidence)” [7]. In clinical practice, surgeons and anesthesiologists usually seek help from opioids [15]. But opioids, taken either before or after the surgery, always produce side effects that can disable physical activities and lower patient satisfaction. Patients with a history of chronic opioid use who successfully decreased their intake of opioids before TKA had substantially improved clinical outcomes that were comparable to patients who did not use opioids at all [16]. At postoperative day (POD) 1 after TKA, at least 25% of patients showed an Opioid-Related Symptom Distress Scale score > 1 for nausea, drowsiness, itchiness and fatigue [15, 17]. Long-term postoperative use of opioids may lead to opioid-induced hyperalgesia (OIH), a paradoxical response to opioids [13, 18, 19]. OIH may reduce opioid efficacy and exacerbate the pain [16].

### Advantages of transcutaneous electrical acupoint stimulation

Given the side effects of opioids, the nonpharmacological approach has been developed as an adjuvant therapy to reduce pain. Transcutaneous electrical nerve stimulation (TENS) is an economical and non-invasive technique [20, 21] with few side effects [14, 22]. TENS with electrodes placed on various acupoints is also called transcutaneous electrical acupoint stimulation (TEAS) [23]. Compared with conventional acupuncture, TEAS brings no risk of needle-induced infection and is more acceptable for those fearing needle stimulation [24]. Evidence has proven that TEAS can effectively reduce postoperative acute pain, the consumption of opioids and opioid-related side effects, and improve patient satisfaction, physical function, and promote the enhanced recovery after surgery (ERAS) [15, 25, 26].

### Objectives

To evaluate the efficacy of different frequencies of TEAS on acute pain after the TKA.

## Methods/design

A mono-center, prospective, randomized, parallel-controlled, participants-, assessor- and statistician-blinded study will be carried out to find the optimal analgesic frequency of TEAS by comparing the efficacy of different frequency on postoperative acute pain control in patients undergoing the primary unilateral TKA. This study strictly followed the principles of the Declaration of Helsinki. The study protocol had been approved by the Clinical Trial Ethics Committee of the Shanghai Guanghua Hospital of Integrated Traditional Chinese and Western Medicine (approval number: 2017-k-41-01) and registered at the Chinese Clinical Trial Registry (http://www.chictr.org.cn/listbycreater.aspx, ChiCTR1800016347). The researchers will be trained in the consistency of the symptoms and signs, the evaluation process.

### Eligibility criteria

The inclusion criteria: (1) 50–80 years old; (2) diagnosis of KOA; (3) prepared to undergo primary unilateral TKA; (4) treated with the same TKA procedures; (5) be American Society of Anesthesiologists (ASA) grades I–II; (6) treated with standard general anesthesia. The exclusion criteria: (1) hyposensitivity or impairment in the leg that was operated on; (2) having used opioids for more than 2 weeks within the preoperative 6 months; (3) having received other nonpharmacological treatments within the preoperative 2 weeks that might affect the outcomes; and (4) showing TENS contraindications, including the use of pacemakers or being allergic to nickel.

### Sample size

The sample size will be calculated using pain ratings from the previous studies [27–29]. The formula:$$ n=\frac{2{\left({Z}_{\alpha }+{Z}_{1-\beta}\right)}^2{\sigma}^2}{\Delta ^2} $$

An effect size (△) of 2 with a standard deviation (SD) of 2.88 between low-frequency (LF) TEAS and placebo-TEAS (*n* = 33 × 4/0.85 = 156), an △ of 2.35 with a SD of 2.56 between high-frequency (HF) TEAS and placebo-TEAS (*n* = 19 × 4/0.85 = 95), an △ of 1.1 with a SD of 0.7 between mixed TEAS and placebo-TEAS (*n* = 7 × 4/0.85 = 35) [26]. Using this information, a four-group study will be established: 33 patients in each group, α = 0.05 (two-sided), β = 0.2 (80% power) [30]. Considering a possible sample loss of 15%, the final sample size will be set with 39 patients in each group.

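### The 80% power stated for the four-group study holds for 5 Hz and 100 Hz against placebo, but not for mixed TEAS against placebo on a common SD, and the frequency-against-frequency contrasts are not sized

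*Protocol article*

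**What the plan says.** All inputs are in the Sample size section of the protocol article. It takes them from earlier work ("The sample size will be calculated using pain ratings from the previous studies [27–29", with a further study cited for the mixed comparison) and gives a separate effect and SD for each active arm against placebo:

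- 5 Hz: an effect "of 2 with a standard deviation (SD) of 2.88 between low-frequency (LF) TEAS and placebo-TEAS", giving 33 per group and a total of 156.
- 100 Hz: an effect "of 2.35 with a SD of 2.56 between high-frequency (HF) TEAS and placebo-TEAS", giving 19 per group and a printed total of 95.
- Mixed: an effect "of 1.1 with a SD of 0.7 between mixed TEAS and placebo-TEAS", giving 7 per group and a printed total of 35.

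The largest result is adopted: "33 patients in each group, α = 0.05 (two-sided), β = 0.2 (80% power". Attrition is then added: "Considering a possible sample loss of 15%, the final sample size will be set with 39 patients in each group".

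The opening of Methods/design gives the purpose as "to find the optimal analgesic frequency of TEAS by comparing the efficacy of different frequency", and the Background of the abstract also names finding the optimal frequency as the aim. The Discussion of the abstract states, before any results exist: "Mixed TEAS has more favorable effect on acute pain control than the placebo or 5 Hz or 100 Hz TEAS".

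**The concern.** The printed formula uses a single σ for both arms of a comparison. All three comparisons share the placebo group, and pain is rated on one 0–10 scale (Pain intensity section). That group will have one variance, so 2.88, 2.56 and 0.7 cannot all describe this trial. The first two are close. The third is about a quarter of them, a 13- to 17-fold difference in variance, and it is the only reason that the smallest assumed effect appears to need the fewest patients.

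Separately, the calculation contains no contrast between two active arms, although comparing frequencies is the reason for the trial.

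A reader who takes 80% power to cover the whole four-group study could read a non-significant mixed-versus-placebo or frequency comparison as evidence of no difference, when the trial had little chance of detecting the difference assumed.

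**Working it through.** **1. Reproducing the plan.** With n = 2(1.96 + 0.8416)²σ²/Δ²:

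- 5 Hz: 2 × 7.849 × 2.88² / 2² = 32.6, so 33.
- 100 Hz: 2 × 7.849 × 2.56² / 2.35² = 18.6, so 19.
- Mixed: 2 × 7.849 × 0.7² / 1.1² = 6.4, so 7.

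All three per-group figures reproduce. So do 33/0.85 = 38.8 (39 per group) and 33 × 4/0.85 = 155.3 (156).

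The other two totals do not: 19 × 4/0.85 = 89.4 (90, printed 95) and 7 × 4/0.85 = 32.9 (33, printed 35). The printed values match division by 0.80: 76/0.80 = 95 and 28/0.80 = 35.

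**2. Placebo contrasts on a common SD.** With 33 per arm, SE = SD × √(2/33), which is 0.630 at SD 2.56 and 0.709 at SD 2.88. Power is for a two-sided t-test at 0.05; the normal approximation is about one percentage point higher.

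| Contrast with placebo | Δ | Power, SD 2.56 | Power, SD 2.88 |
|---|---|---|---|
| 5 Hz | 2.0 | 88% | 79% |
| 100 Hz | 2.35 | 96% | 90% |
| Mixed | 1.1 | 41% | 33% |

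By the plan's formula, 5 Hz at SD 2.88 has 80.5%, which is the design value. For 80% power, mixed versus placebo needs 2 × 7.849 × 2.56²/1.1² = 85.02 (86 per arm) or 2 × 7.849 × 2.88²/1.1² = 107.6 (108 per arm).

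**3. Sensitivity: SD 0.7 in the mixed arm only.** SE = √((0.7² + 2.88²)/33) = 0.516, or 0.462 with 2.56. Mixed versus placebo then has 56% or 65% power.

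**4. Active-versus-active contrasts.** The difference detectable with 80% power is 2.8016 × SD × √(2/33) = 1.77 points at SD 2.56 and 1.99 at SD 2.88. This needs no assumption about the true differences between frequencies.

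*Assumption, not a figure in the plan:* subtracting the stated placebo effects gives differences of 2.35 − 2.0 = 0.35, 2.0 − 1.1 = 0.9 and 2.35 − 1.1 = 1.25. Power with 33 per arm is then:

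| Contrast | Δ (assumed) | SD 2.88 to 2.56 in both arms | SD 0.7 in the mixed arm only |
|---|---|---|---|
| 100 Hz vs 5 Hz | 0.35 | 8–9% | not applicable |
| 5 Hz vs mixed | 0.9 | 24–29% | 40–48% |
| 100 Hz vs mixed | 1.25 | 41–50% | 66–76% |

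**The case against.** The best defence is that the SDs are planning inputs quoted per comparison from separate studies. The article does not say whether those studies share this trial's scale, time point or type of SD. Taking the largest of three sample sizes is a normal cautious step, and 0.7 did not set N. This stands as far as it goes: N = 156 follows from the 5 Hz inputs. But different sources explain the mismatch without removing it, because this trial will have a single placebo variance.

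Several stronger readings are tempting, and the document does not support them:

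- *That only 5 Hz versus placebo is powered.* 100 Hz versus placebo keeps about 90–96%.
- *That the true placebo SD is 2.88.* The article states no placebo SD, and 2.56 has equal standing. Hence the range.
- *That 8–50% is the plan's own power for the frequency contrasts.* It rests on subtracting effects from separate studies and on SD 2.56–2.88. With SD 0.7 in both arms, the two mixed contrasts would exceed 99%, though that contradicts the SDs stated for 5 Hz and 100 Hz.
- *That the plan's effects rank mixed lowest and so refute its hypothesis.* Raw effects from separate studies are a weak basis for ranking. Standardised, the order reverses: 1.1/0.7 = 1.57, against 2.35/2.56 = 0.92 and 2/2.88 = 0.69. The main Discussion also reports that the study cited for the mixed input found mixed stimulation better than 2 Hz or 100 Hz alone.
- *That the article claims power for the frequency contrasts and the claim is false.* It attaches its calculations to placebo contrasts. The accurate statement is that the frequency contrasts are not sized.

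The Statistical analysis section also plans a repeated-measures model, which may gain some precision over the single-time-point test used here. The gain cannot be computed from the article.

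**Conclusion.** The concern holds in this limited form. The stated 80% power is met for both single-frequency arms against placebo. It is not met for mixed versus placebo, the arm that the hypothesis favours: about 33–41% on a common SD of 2.56–2.88, and about 56–65% if the mixed arm alone has SD 0.7. No scenario that gives the placebo arm either of the other two stated SDs reaches 80%.

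The contrasts between frequencies are unsized. The smallest difference they can detect with 80% power, 1.8–2.0 points, is close to the whole effect assumed for 5 Hz over placebo.

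These figures assume 33 evaluable per arm, two-sided 0.05 per contrast and a comparison at one time point. The totals 95 and 35 are arithmetic slips without consequence for N.

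**What to change.** Keep N = 156 and make these changes of wording:

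1. In the Sample size section, base the power statement on one common SD with a sensitivity range (2.56 to 2.88 on the article's own figures). Give the detectable difference for 33 evaluable per arm and the power for mixed versus placebo and for each active-versus-active contrast, with any assumed differences between frequencies labelled as assumptions.
2. Correct 95 to 90 and 35 to 33.
3. State that a non-significant frequency contrast will be reported with its 95% confidence interval and will not be read as equivalence. At these SDs the half-width is about 1.3 to 1.4 points (t quantile 2.00 × 0.630 to 0.709).
4. Reword the sentence in the Discussion of the abstract as a hypothesis.

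No extra patients or procedures are needed. The cost is that the stated power becomes less favourable.

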### Recruitment strategies and enrollment

KOA inpatients who are scheduled to undergo a primary unilateral TKA between May 2018 to May 2019 will be recruited by the Department of Joint Surgery, the Shanghai Guanghua Hospital of Integrated Traditional Chinese and Western Medicine. The main recruiting mode will be propagated by a resident doctor (A). The KOA inpatients willing to participate in our study will be screened by specific researchers (B). The inpatients who meet the screening criteria will be clearly aware of their involvement in this study. The participant who needs to be transferred to the intensive care unit after a standard TKA procedure or perioperative interference will be excluded. These participants often have some complications of other organ systems, including cardiopulmonary insufficiency or damaged liver or kidney function, which may interference the baseline characteristics of the participant of this clinical trial. Those participants who transfer to the general ward will be asked to provide informed consent.

Figure 1 shows the trial flow chart for the patient screening, treatment allocation, intervention, outcomes assessment and data analysis. Figure 2 provides an overview of the study conduct, review, description and interpretation. The populated Standard Protocol Items: Recommendations for Interventional Trials (SPIRIT) Checklist is presented in Additional file 1.

**Fig. 1 Fig1:**
[figure not shown]
The trial flow chart

**Fig. 2 Fig2:**
[figure not shown]
The schedule of trial enrollment, interventions and assessments

### Randomisation and allocation concealment

Participants who meet the screening criteria will be randomized into four balanced groups: G1, G2, G3 and G4. The randomization sequence will be computer-generated by an independent research staff (C) with a 1:1:1:1 ratio using SPSS 21.0.

At POD 3 and before the TEAS application, three physical therapists (D, E, F) will be mainly responsible for the treatment sessions and outcomes evaluation. Initially, D will perform the basic measurements of participants in four groups and double-check whether the sensation in the leg that was operated on is normal. After D leaves the ward, E will apply a 30-min TEAS intervention and subsequently F will perform a 30-min rehabilitation session per day in four groups. One TEAS intervention and one rehabilitation constitute one treatment session. Immediately after the end of one treatment session, D will return to the ward, evaluate and record the outcomes according to the trial design. Researchers except for C and E will be blinded to the treatment allocation. Randomisation and allocation concealment in a light-tight sealed envelope until E firstly reveals the TEAS intervention according to the random number sequence at POD 3. Participants will be required not to communicate with any other researchers, participants and care providers to minimize the risk of potential bias. After the latest TEAS intervention, participants and outcome assessors will be asked to guess whether the subjects received active TEAS or placebo TEAS within 5 min to evaluate the blinding quality.

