### Outcomes evaluations

Pain intensity (rest and movement) and the American Knee Society Score (AKSS) are the primary outcomes. Secondary outcomes include active range of motion (AROM) of the knee that was operated on, surface electromyography of both quadriceps, the modified 30-s sit to stand test, additional use of analgesics and the 36-item Short Form health survey (SF-36). The additional outcomes include patient satisfaction rate, patient expectation rate and the incidence of analgesia-related side effects.

The pain intensity, AROM, incidences of analgesia-related and TEAS-related side effects will be daily recorded. Evaluation of the patient satisfaction rate and patient expectation rate will be conducted after the first episode of the TEAS intervention. The SF-36 will be evaluated at two time points: before the TEAS intervention, and 2 weeks after the TEAS intervention. The assessment time points of the remaining outcomes are before the surgery, after the surgery before the TEAS intervention(at POD 3), and 1 week and 2 weeks after the TEAS intervention.

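### As written, patient and assessor guess the allocation before the final pain and AKSS scoring; the guess should follow it

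*Protocol article*

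**What the plan says.** The section Randomisation and allocation concealment sets the order of a treatment day. Therapist D takes the baseline measurements and leaves the ward. Then "E will apply a 30-min TEAS intervention and subsequently F will perform a 30-min rehabilitation session per day in four groups". The section defines its terms: "One TEAS intervention and one rehabilitation constitute one treatment session". Scoring follows the session as a whole: "Immediately after the end of one treatment session, D will return to the ward, evaluate and record the outcomes according to the trial design".

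The blinding check is tied to TEAS, not to the session: "After the latest TEAS intervention, participants and outcome assessors will be asked to guess whether the subjects received active TEAS or placebo TEAS". The limit for this is 5 min, and the purpose is to judge how well blinding worked. The abstract (Methods/design) drops the word TEAS and says of participants and assessors that "they are asked to guess whether the subjects received active or placebo TEAS within 5 min after the latest intervention".

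Under Outcomes evaluations, "Pain intensity (rest and movement) and the American Knee Society Score (AKSS) are the primary outcomes". Pain is recorded daily. AKSS is taken before surgery, on POD 3 before TEAS, and at weeks 1 and 2.

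**The concern.** Asking someone to name the treatment makes them settle on a belief. If the question comes before a subjective rating, that belief can colour the rating.

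Both primary outcomes are open to this. The NRS is the patient's own report. The AKSS is scored by the assessor, and pain carries 50 of the 100 points in its knee part. Both people are asked to guess.

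Guesses may also differ by arm. Under TEAS interventions, the placebo current runs for 30 s and fades over the next 15 s, while the active arms are stimulated for 30 min. An effect of answering the question need not cancel between active and placebo. The Discussion faults earlier trials for weak control of blinding and says that it is strictly controlled here, so a check that could itself disturb the final ratings works against the trial's own aim.

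**Working it through.** The point is one of sequence. The plan gives no figure for it, and the sample size does not enter.

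**Inputs**, all from Randomisation and allocation concealment: TEAS lasts 30 min; rehabilitation follows for 30 min; D scores once the session has ended; the guess is due within 5 min after the last TEAS.

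**Reading 1, literal.** Minutes are counted from the start of the last TEAS.

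| Step | Minutes |
|---|---|
| TEAS | 0 to 30 |
| Allocation guess | 30 to 30 + 5 = 35 |
| Rehabilitation | 30 to 30 + 30 = 60 |
| Scoring by D | from 60 |

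Gap from guess to start of scoring: 60 − 35 = 25 min to 60 − 30 = 30 min. The table takes rehabilitation to start as soon as TEAS ends. A pause between them would lengthen the gap.

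**Reading 2, the abstract's looser wording.** If the latest intervention means the whole session, the guess is due between 60 and 60 + 5 = 65 min, just as D begins. Resting pain is to be taken ahead of other procedures, so it might be recorded first. The remaining work includes the AKSS stability, alignment and extension-lag tests, AROM in triplicate, and the sit-to-stand test with surface EMG. In my judgement this would not be finished in 5 min, so the guess would fall before or during much of the scoring.

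**Reading 3, week 2 counted from the last TEAS.** Outcomes evaluations can be read as placing the last assessment two weeks after the TEAS course. The guess would then precede the week-2 ratings by about two weeks.

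**Comparison.** The interval runs from none to about two weeks, but no reading puts the guess after the final ratings are complete.

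**The case against.** The best defence is that the literal order was probably not intended. D leaves before TEAS starts and returns only when the session is over, so a literal reading has D guessing while off the ward. The authors may well have meant the end of the last session. The schedule in Fig. 2 is not available here and might show this. That stands as a reason for caution about intent, but the two passages that fix the timing do not say it, and the end-of-session reading still does not put the guess after scoring.

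A second defence is that exposure is narrow: the question can touch only ratings made after it. Pain is recorded daily and repeated measures go into a longitudinal model, so most pain data are collected beforehand. This stands as well. The protocol names no main time point, so one cannot say that the decisive comparison is hit.

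A reader might go further in three ways that the document does not support:

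- **A numerical bias.** Any figure in NRS points would need an assumed shift and assumed guess rates by arm. It would also charge to the question a belief that patients hold whether or not they are asked. Only the increment from being asked matters, and nothing here sizes it.
- **An uninterpretable blinding check** because there are three active arms to one placebo arm. The protocol never proposes pooled percent correct or a 50% benchmark. Guesses can be tabulated by arm, and the choice of index is normally left to the analysis plan.
- **A missing early guess.** One guess at the end of treatment is a legitimate choice. Adding one after the first session would expose far more ratings to the very effect at issue.

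**Conclusion.** The concern holds as a point about order. Followed as written, the blinding question precedes the last session's scoring by about 25 to 30 min. On the other readings it falls at the start of that scoring, or about two weeks before the week-2 assessment. Patient and assessor therefore state a belief before the final NRS and AKSS are rated.

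The conclusion rests on the section's own distinction between a TEAS application and a treatment session, and on the absence of any statement that the guess follows the ratings. It covers only ratings made after the question. Earlier daily pain scores are unaffected, and so are the week-1 ratings where week 1 falls within the treatment course. The direction and size of any bias are unknown. The point is worth correcting because the exposure touches both primary outcomes and is easily removed, not because a material bias has been shown.

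**What to change.** In the abstract and in Randomisation and allocation concealment, state that participants and the assessor are asked for their guess only after D has recorded all final (week-2) outcomes. Use the same wording in both places, and say whether week 2 is counted from the first or the last TEAS, so that the moment of the question is unambiguous.

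If week 2 ends the treatment course, the cost is moving one question by roughly the length of the rehabilitation plus the scoring. If week 2 lies two weeks after the last TEAS, the guess moves to that visit and relies on longer recall. In either case the 5-min limit after TEAS goes, and the guess will be made with the last ratings fresh in mind. That is a small price for keeping the ratings free of the question. Sample size, visits and outcome analyses stay as they are.
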